### Data Management

Outcome assessors at each center recorded all study data. These assessors received standardized training prior to participant recruitment. The training covered procedures for accurately and promptly completing case report forms (CRFs) and electronic CRFs. Standard operating procedures were established and made available to investigators and assessors at each trial site.

Investigators were not permitted to modify or access data until enrollment, follow-up, and data collection had been completed for all participants.

### Statistical Analysis

The primary outcome—the ACR20 response rate at week 12—will be compared between each combination therapy group and the TGT monotherapy group using logistic regression. The study center will be included as a fixed effect to account for potential site differences.

Secondary outcomes (eg, DAS28-ESR and CDAI) will be analyzed using mixed-effects models for repeated measures. These models will include fixed effects for treatment, visit, treatment-by-visit interaction, baseline value, and study center, with participants included as a random intercept.

All primary analyses will be conducted on the intention-to-treat population, defined as all randomized participants who received at least 1 dose of the study drug. Missing data will be handled using multiple imputation under the missing-at-random assumption, generating 20 imputed datasets. Sensitivity analyses will be performed to evaluate the robustness of conclusions under different missing data assumptions.

Safety data, including adverse events, will be summarized descriptively by treatment group. Between-group comparisons of adverse event rates will be conducted using the Fisher exact test.

Rescue therapy with NSAIDs was permitted for intolerable joint pain, in line with ethical requirements and standard clinical practice for the management of RA. As pain and swelling are universal symptoms of active RA, the requirement for rescue analgesia reflects real-world treatment conditions and will not be statistically adjusted in the primary analysis. The use of rescue medication will be documented descriptively and reported by treatment group. If notable between-group differences in the frequency of rescue therapy are observed, exploratory sensitivity analyses will be conducted to assess their potential influence on efficacy outcomes.

All analyses will be performed using SAS (version 9.4) and R (version 4.4.s2; R Foundation for Statistical Computing). Between-group differences will be reported with 95% CIs. Statistical significance is set at α=.05 (2-sided).

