### Outcome Measures

#### Primary Outcome Measurement

The American College of Rheumatology 20% improvement (ACR20) response rate at week 12 is defined as ≥20% improvement in both tender joint count (TJC) and swollen joint count (SJC), as well as ≥20% improvement in at least 3 of the following 5 domains: patient global assessment (PGA), medical doctor global assessment (MDGA), patient pain visual analog scale (VAS), Health Assessment Questionnaire Disability Index (HAQ-DI), and acute-phase reactants (erythrocyte sedimentation rate [ESR] or C-reactive protein [CRP]).

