### Sample Size

The sample size was calculated for a multicenter RCT with 1 common control group (TGT monotherapy) and 3 active treatment groups (TGTs+methotrexate, TGTs+hydroxychloroquine, and TGTs+leflunomide). The primary hypothesis is that each combination therapy will be superior to TGTs monotherapy for the ACR20 response rate at week 12. The assumed ACR20 response rates were derived from an unpublished study conducted at our center in 2022 ([name], unpublished data, May 2022). This study included 30 patients with moderate RA (DAS28 3.2-5.1), randomized 1:1 to receive either TGT monotherapy (n=15) or TGTs+methotrexate (n=15) for 12 weeks. The observed ACR20 response rates were 53.3% (8/15) in the monotherapy group and 80% (12/15) in the combination group. On the basis of these data, the following assumptions were made:

TGT monotherapy—ACR20 response rate=54%

Combination therapy (TGTs+methotrexate, TGTs+hydroxychloroquine, and TGTs+leflunomide)—ACR20 response rate=80%

We consider this absolute difference of 26 percentage points to be clinically meaningful.

The sample size calculation was performed using PASS (Power Analysis and Sample Size) software (version 15; NCSS, LLC). The procedure selected was “chi-square tests” to compare multiple treatment groups with a common control while controlling the family-wise type I error rate.

Input parameters included the following: solving for sample size, degree of freedom 3; power 0.8; α=.05, and effect size (w=0.255098).

Consequently, the Dunnett procedure required 42 participants per group, resulting in a total sample size of 168 before accounting for dropouts. With an estimated dropout rate of 10%, the adjusted total sample size was approximately 188 participants, corresponding to approximately 47 participants per group.

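### The primary ACR20 model is valid with centre alone, but adding baseline DAS28-ESR and reporting a standardised risk difference would make it somewhat more precise and easier to read against the 26-point target

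*Protocol article*

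**What the plan says.** In the Protocol article, Statistical Analysis, the primary outcome "will be compared between each combination therapy group and the TGT monotherapy group using logistic regression". On covariates, that paragraph adds only: "The study center will be included as a fixed effect to account for potential site differences". The repeated-measures models for the secondary outcomes carry "fixed effects for treatment, visit, treatment-by-visit interaction, baseline value, and study center".

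On reporting, the section closes with "Between-group differences will be reported with 95% CIs". It does not give the scale of the ACR20 contrast or say how a difference would be obtained from the logistic model.

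The Sample Size section assumes response rates of 54% on monotherapy and 80% on each combination, and states: "We consider this absolute difference of 26 percentage points to be clinically meaningful". Table 1 schedules DAS28-ESR, DAS28-CRP, CDAI, SDAI and HAQ-DI at baseline. The Abstract (Results) reports that data collection is complete, cleaning is under way and no analysis has yet been done.

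**The concern.** Two separable points arise.

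**Precision.** A baseline measure of disease activity may predict who responds. If it does, including it in the primary model makes better use of the patients already recruited. Enrolment closed at 181, about 45 per arm (181/4 = 45.25), so sample size can no longer be raised and covariate adjustment is one of the few levers left.

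**Interpretability.** The trial's yardstick is an absolute difference, but the named model works on the odds scale. The percentage-point meaning of a given odds ratio depends on the control rate. That rate rests on 8 responders among 15 pilot patients, so it could well differ from 54%. If the headline result were only an odds ratio, a reader could not tell whether the 26-point mark had been met. A reader might also take 3.4 for a ratio of response rates, when 54% versus 80% is a risk ratio of 0.80/0.54 = 1.48.

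**Working it through.** **1. The plan's own figure.** With rates 54/80/80/80%, the mean is (0.54 + 3 × 0.80)/4 = 0.735. The mean squared deviation is (0.195² + 3 × 0.065²)/4 = 0.012675. Then w = √[0.012675/(0.735 × 0.265)] = 0.255098, exactly as stated. A 3-df chi-square test at α = 0.05 with 80% power needs noncentrality 10.903, so N = 10.903/0.255098² = 167.5. That rounds to 168, or 42 per arm. Dropout gives 168/0.9 = 186.7, and 188 for four equal arms. The plan's figures reproduce. The 26 points enter only through the assumed rates.

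**2. Percentage points against odds ratio.** OR = (0.80/0.20)/(0.54/0.46) = 3.41. Holding this OR fixed, the combination rate is p₁ = OR·p₀/(1 − p₀ + OR·p₀):

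| Control rate p₀ | Combination rate p₁ | Difference (points) |
|---|---|---|
| 40% | 69.4% | 29.4 |
| 54% | 80.0% | 26.0 |
| 60% | 83.6% | 23.6 |
| 70% | 88.8% | 18.8 |

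The 40% to 70% range is not far-fetched: a Wilson 95% interval for the pilot's 8/15 runs from about 30% to 75%.

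**3. What adjustment could gain.** The documents give no association between baseline DAS28 and ACR20, so it is an assumption, varied from none to strong. Simulation set-up: four arms of 42, three centres of equal size, 4,000 replicates, overall rates held at 54% and 80%, and a Wald test of one combination against monotherapy. Power is shown for centre only → centre plus baseline.

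| Log-odds per SD of baseline | Adjusted OR equivalent to 54% vs 80% | Two-sided 0.05 | Two-sided 0.05/3 |
|---|---|---|---|
| 0 | 3.41 | 72.9% → 72.8% | 55.0% → 54.6% |
| 0.5 | 3.63 | 73.5% → 75.4% | 54.7% → 57.5% |
| 1.0 | 4.29 | 73.6% → 79.7% | 56.2% → 64.8% |

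The closed-form two-proportion power at 42 per arm is 72.5% at 0.05 and 55.8% at 0.05/3, in line with the centre-only figures.

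A separate two-arm simulation used a Dunnett critical value of 2.349 and 3,000 replicates. For prognostic odds ratios of 1.0, 1.5, 2.0 and 2.5 per SD it gave 58.0 → 57.3%, 57.5 → 57.8%, 57.0 → 60.6% and 57.5 → 63.5%.

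The change is therefore about 0 to 6 points, with a loss of up to about 1 point when the covariate carries no information. Only the most favourable corner goes higher: about 8.5 points at log-odds 1.0 per SD and the 0.05/3 threshold. No scenario reaches 80%.

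**4. How plausible the upper end is.** Textbox 1 admits only DAS28 above 3.2 and up to 5.1, a span of 1.9. If scores were uniform over it (an assumption), the SD would be 1.9/√12 = 0.55. Log-odds of 0.5 and 1.0 per SD would then be odds ratios of about 2.5 and 6.2 per DAS28 unit. The upper figure is very strong, so the lower part of the gain range is the more credible.

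**The case against.** **The centre-only model is sound.** A reader might infer that it is biased, or that chance baseline imbalance invalidates it. It does not: under randomisation the test and interval already allow for such imbalance. What is lost is efficiency. This objection stands.

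**There is no inconsistency with the secondary models.** A reader might infer a contradiction because those models include the baseline value. They adjust each score for its own baseline. ACR20 has none: Primary Outcome Measurement defines it as improvement from baseline, and Table 1 first assesses it at week 4. This stands too.

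**Logistic regression can yield a percentage-point effect.** Standardising the fitted probabilities gives one, and the sentence on between-group differences leaves room for it. The full analysis plan, which is not shown, may name it. It would be wrong to say that the model cannot deliver the target quantity. What remains is that the article sets an absolute target, names a relative-scale model and leaves the link open.

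**The gain is assumed and the change is late.** Both are true. Prognostic strength is unknown, the entry range is narrow, and data collection is finished in an open-label trial. However, outcome adjudicators and analysts are blinded and no analysis has been run, so a dated change is still credible. An adjusted odds ratio also drifts from the unadjusted one (3.41 to between 3.63 and 4.29 above) with the response rates unchanged. That is a reason to lead with the standardised difference.

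**Conclusion.** The point holds as an optional improvement in efficiency and interpretability. It is neither a bias nor a contradiction.

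The interpretability part needs only the assumed rates and arithmetic: an odds ratio of 3.41 corresponds to anything from 18.8 to 29.4 points over control rates of 40% to 70%.

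The precision part is worth about 0 to 6 points of pairwise power, at a risk of about 1 point. It rests on a prognostic strength that the documents do not supply.

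A reader might infer that adjustment would repair the gap between the 3-df sample size and the pairwise comparisons. It would not: pairwise power stays below 80% in every scenario examined.

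**What to change.** Before any unblinded analysis, and in a dated amendment or in the analysis plan:

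- Fit one four-arm logistic model for ACR20 at week 12 with treatment, centre and baseline DAS28-ESR as a continuous covariate.
- For each combination against monotherapy, give the covariate-standardised difference in response rate with its 95% CI as the main effect estimate, and the odds ratio as supportive. Combine estimates over the 20 imputed datasets, and include baseline DAS28-ESR in the imputation model.
- Keep the centre-only model as a sensitivity analysis.

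The two parts can be adopted separately: a standardised risk difference from the centre-only model would by itself settle the question of scale.

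The cost is a sentence or two of text and a few lines of code, with no new data. The real price is a documented late change to the primary analysis, so the date and the blinded status of the analysts should be recorded with it.

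### The sample-size section claims family-wise error control over three comparisons with a common control, but the primary analysis tests each at two-sided 0.05, giving about a 12% chance of a false positive

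*Protocol article*

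**What the plan says.** The Sample Size section sets up "1 common control group (TGT monotherapy) and 3 active treatment groups" and states the claim to be tested: "The primary hypothesis is that each combination therapy will be superior to TGTs monotherapy for the ACR20 response rate at week 12". It says the software procedure was chosen "to compare multiple treatment groups with a common control while controlling the family-wise type I error rate", lists the inputs as "degree of freedom 3; power 0.8; α=.05, and effect size (w=0.255098", and concludes that "the Dunnett procedure required 42 participants per group, resulting in a total sample size of 168 before accounting for dropouts".

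The Statistical Analysis section is the only analysis text in the protocol. It says the week-12 ACR20 response "will be compared between each combination therapy group and the TGT monotherapy group using logistic regression", with centre as a fixed effect. It closes with two general statements: "Between-group differences will be reported with 95% CIs", and "Statistical significance is set at α=.05 (2-sided". No multiplicity procedure appears in that section or in any other description of the analysis.

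**The concern.** The two sections describe different error control for the same three primary comparisons. The first claims protection across the family and names the method. The second specifies the model, the interval level and the significance level, and leaves the protection out. An analyst who followed the Statistical Analysis section would run three contrasts, call any with p<0.05 significant, and report ordinary 95% intervals.

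This matters because the trial has three routes to a positive headline. The abstract's objective is to find the optimal combination, so one significant arm out of three is enough for a claim. A reader of the Sample Size section would take an isolated p=0.03 as protected against multiplicity when it is not.

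**Working it through.** **1. Reproduce the protocol's own figure.** Inputs from Sample Size: ACR20 rates 54% (monotherapy) and 80% (each combination), 3 degrees of freedom, α=0.05, power 0.80.

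- Mean rate: (0.54 + 3×0.80)/4 = 0.735.
- Mean squared deviation: (0.195² + 3×0.065²)/4 = (0.038025 + 0.012675)/4 = 0.012675.
- w = √[0.012675 / (0.735×0.265)] = √0.065075 = 0.255098, the stated value.
- A 3-df chi-square test with noncentrality N·w² reaches 80% power at N = 168 (power 0.801), which is 42 per group. With 10% dropout, 42/0.9 = 46.7, so 47 per group and 188 in total.

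The stated size therefore reproduces exactly, but as a four-group omnibus chi-square test. It is not a Dunnett calculation, and the omnibus test does not appear in Statistical Analysis. The claimed family-wise control is thus delivered neither by the sizing calculation nor by the analysis.

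**2. Family-wise error of the analysis as written.** With 1:1:1:1 allocation and no true differences, each contrast has variance 2σ² and any two share the control's σ², so their correlation is σ²/2σ² = 0.5. The chance that at least one of three |Z| exceeds c is

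1 − ∫ φ(x) [Φ((c − √0.5·x)/√0.5) − Φ((−c − √0.5·x)/√0.5)]³ dx.

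At c = 1.96:

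| Quantity | Result |
|---|---|
| At least one two-sided p<0.05, either direction | 12.5% |
| At least one significant result favouring a combination | 6.3% (one test: 2.5%) |
| For reference, independent tests: 1 − 0.95³ | 14.3% |
| Bonferroni bound: 3×0.05 | 15% |

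Both error rates are about 2.5 times the single-test level: 12.5/5 = 2.5 and 6.3/2.5 = 2.5.

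**3. Finite-sample check.** This used 400,000 simulated trials with Wald tests of the log odds ratio and no centre term. With 47 per group, at least one test was significant in 12.2% of trials at a common rate of 54% and in 11.7% at 80%. With 42 per group the figures were 12.3% and 10.6%. Score tests on the same data ranged from 12.3% to 15.4%. In the superiority direction, results across all these settings lay between 5.3% and 7.7%.

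**4. What the named procedure would do.** Setting the expression in step 2 to 0.05 gives a Dunnett critical value of 2.349, or 0.0188 two-sided per comparison. Bonferroni would use 0.05/3 = 0.0167.

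Power per comparison, 54% vs 80%, is Φ{[0.26 − c·√(2×0.67×0.33/n)] / √[(0.54×0.46 + 0.80×0.20)/n]}:

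| n per group | c = 1.96 | c = 2.349 |
|---|---|---|
| 42 | 72% | 58% |
| 45 (181 enrolled / 4 = 45.25) | 75% | 61% |
| 47 | 77% | 63% |

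Power of 80% per comparison under Dunnett would need about 66 per group: 264 in total, or 264/0.9, about 294, with 10% dropout.

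**The case against.** The strongest reply is that Statistical Analysis never says the tests are unadjusted. Its significance sentence is a general closing line, and 0.05 could be the family-wise level, as it seems to be in Sample Size. On that reading Dunnett has been named once and not repeated, and the details may sit in an analysis plan that is not shown. This reading is possible but is not written. The section gives a test, an interval level and a significance level for each contrast, and applied literally they do not produce family-wise control. The point is a mismatch between two sections, not a detail left for later. If Dunnett is intended, the remedy is still to say so where the analysis is defined.

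A second reply is that no adjustment is needed if success requires all three combinations to win. The Sample Size hypothesis refers to each combination, and the Discussion expects all three to be superior. However, neither section makes joint success the decision rule, and the aim of picking the best regimen points the other way. The protocol itself chose family-wise control.

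A third reply concerns the headline figure: 12% counts results in either direction, while the practical harm is a false superiority claim. That is correct. The superiority figure is about 6%, although the inflation ratio is the same. It also stands that the cost in power is substantial now that enrolment has closed.

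**Conclusion.** The concern holds. The protocol claims family-wise error control for its primary comparisons, and the analysis it specifies does not provide it. The error rate is 12.5% for any false positive and 6.3% for a false superiority claim. These figures assume that no combination differs from monotherapy, that the arms are equal in size, that any one significant arm counts as a finding, and that the 0.05 level applies to each contrast as the text reads. The simultaneous coverage of the three ordinary 95% intervals falls short in the same way. This is the decision rule for the primary outcome, so it should be settled before the data are analysed.

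**What to change.** Rewrite the primary-analysis paragraph to carry out the commitment made in Sample Size:

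- Fit one logistic model with all four arms and centre.
- Declare the three contrasts against TGT monotherapy as the primary family, and state that 0.05 two-sided is the family-wise level.
- Test them with a Dunnett adjustment (critical value about 2.35). Holm is an acceptable fallback if Dunnett is awkward to apply after multiple imputation.
- Report simultaneous 95% intervals for these three contrasts. With the Dunnett value they are about 20% wider on the log-odds scale (2.349/1.96 = 1.198).
- State that secondary outcomes are unadjusted and supportive.

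In text this costs one paragraph. The protocol reports that no statistical analysis has been done and that the analysts are blinded to allocation, so the change can still be made and dated without knowledge of results. The real cost is power per comparison, which falls to about 61% at the enrolled size (about 45 per group) and 58% at 42 per group under the protocol's own assumed rates. Recruitment is closed, so this cannot be recovered by enrolling more patients. The protocol should disclose it, so that a non-significant contrast is not read as evidence of no benefit.

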### Quality Control

All investigators received specific training on trial objectives, protocols, treatment strategies, and quality control procedures before the trial commenced. All investigators involved in this study were rheumatologists with at least 5 years of clinical experience.

All trial documents, including screening forms, CRFs, and treatment records, are stored at the study site under locked conditions with restricted access.

Every 3 months, members of the quality monitoring team will conduct on-site quality control reviews at each participating site and generate reports on the overall quality of the study processes. Trial managers will hold regular meetings to discuss and address any issues identified during monitoring.

### Ethical Considerations

The Dongzhimen Hospital Ethics Committee of Beijing University of Chinese Medicine approved the study protocol (2024DZMEC-241). The trial is conducted in accordance with the Declaration of Helsinki and is registered with the Chinese Clinical Trial Registry.

Each participant was informed of the study’s purpose, potential risks, and benefits. The recruiting physician reviewed the written informed consent form with the participant. Participants did not receive any financial compensation for their involvement in this study, as the trial involved only marketed drugs with well-established safety and efficacy profiles, and no additional procedures beyond routine clinical practice were required.

In this study, personal identifying information was removed and replaced with a unique, nonidentifiable code. No personal information was transmitted, ensuring data confidentiality. The results of this study will be presented at selected conferences and scientific meetings and published in peer-reviewed journals. To promote transparency, the original dataset will be shared with external researchers upon reasonable request, beginning three years after the main results are published.

## Results

Recruitment began on September 1, 2024, and ended on December 31, 2025, with a total of 181 patients enrolled. Final data collection has been completed, and data cleaning is underway. Results are expected to be published by the end of 2026.

## Discussion

### Summary of Anticipated Findings

This trial is expected to provide robust evidence on the comparative efficacy and safety of TGT-based combination therapies in patients with moderately active RA. We hypothesize that all 3 TGT combination regimens (TGTs+methotrexate, TGTs+hydroxychloroquine, and TGTs+leflunomide) will result in significantly higher ACR20 response rates at week 12 than TGT monotherapy. These findings are expected to clarify the risk-benefit profile of these combinations and identify which regimen offers the most favorable balance of efficacy and tolerability for different patient subgroups.

